### Surgical technique

During several face-to-face meetings of the participating surgeons, agreement was reached regarding the (oncological) standards that should be followed during both minimally invasive and open distal pancreatectomy. Previously published and renowned standards for oncological distal pancreatectomy (formally called a left pancreatectomy) were followed; these standards were substantially described by Strasberg et al. [25] for the open approach and by Abu Hilal et al. [26] for the minimally invasive approach, including:
Gerota’s fascia: routine resection of Gerota’s fascia should be performed in all patients.Splenectomy: should be performed in all patients.Lymphadenectomy: the ISGPS criteria for lymph node resection [27] will be followed. This includes resection of lymph node stations 10, 11, and 18 for tumors of the pancreatic body and tail. Additional resection of stations 8 and 9 will be performed when tumors affect the body of the pancreas. The aim is to resect a minimum of 11 lymph nodes.Transection of the pancreas: will be performed at the neck of the pancreas. The use of a stapling device is preferred but not mandatory as long as the same method is used in MIDP and ODP in each individual center.Transection of the splenic artery and vein: the use of clips (e.g., hem-o-lok, regular metal clips), staples, or sutures is not mandatory as long as the same method is used in MIDP and ODP in each individual center.Frozen sections: sampling of frozen sections is not mandatory, but surgeons should follow the same routine in both MIDP and ODP in each individual center.Surgical margins: sutures will be used to mark all surgical [transection (neck of the pancreas), posterior (Gerota’s fascia), and anatomical (anterior (peritonealised) and superior)] margins.

No specific other standards for MIDP and ODP are provided. Several of the above-mentioned details (e.g., regarding the method of transection of the pancreas and splenic artery and vein) are also relevant for the blinding of pathologists. All procedure details will be recorded within the case report form.

### Conversion from MIDP to ODP

Any incision used for other reasons than trocar placement or specimen extraction is defined as a conversion. Patients allocated to MIDP but converted to ODP will still be analyzed in the MIDP group, according to intention-to-treat principles. Reasons for conversion will be registered and categorized as urgent or non-urgent conversions [28].

### Blinding

Within the DIPLOMA trial, all assessors of the primary outcome (i.e., the pathologists), the patients, and the adjudication committee are blinded for treatment allocation. Directly after skin closure, while still under general anesthesia, patients will receive a firmly taped, large 40 × 40 cm abdominal dressing to cover their incision(s) and therefore their treatment allocation (minimally invasive or open). This abdominal dressing will be removed when all criteria for functional recovery are met or earlier for medical reasons, such as suspicion of wound infection. If earlier inspection is required, attempts are made to maintain patient blinding. This blinding has proven to be successful in previous multicenter trials [5, 29, 30]. The success of blinding will be assessed using the blinding index as proposed by Bang et al. [31]. Both patients and pathologists will be asked about the alleged treatment allocation, based on five categories: (1) strongly believe it was MIDP, (2) somewhat believe it was MIDP, (3) somewhat believe it was ODP, (4) strongly believe it was ODP, and (5) do not know. Due to ethical and legal concerns, patient blinding will not be performed in participating centers from the USA and in patients who are intra-operatively diagnosed with irresectable disease, such as metastases. Since patient blinding only influences one of the secondary outcomes, time to functional recovery, and not the primary outcome, this is considered of minor influence. Sensitivity analysis, excluding centers from the USA and patients with perioperative diagnosed metastasized disease will be performed for analysis of time to functional recovery.

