## Background

Several randomized trials have suggested superiority of minimally invasive surgery over open surgery in terms of postoperative pain, morbidity, and length of hospital stay [1–5]. Minimally invasive distal pancreatectomy (MIDP), first described by Gagner in 1996 [6], is considered the standard approach for symptomatic benign and premalignant disease of the distal pancreas in many centers around the world [7, 8]. Although the number of pancreatic resections performed through a minimally invasive approach increased significantly during the past two decades, the initial introduction of minimally invasive pancreatic surgery has been rather slow [9, 10]. Recently, the first single- and multicenter, randomized, controlled trials comparing MIDP with open distal pancreatectomy (ODP) showed clear benefits of MIDP in terms of less intra-operative blood loss, a 2-day reduction in both time to functional recovery and length of hospital stay, and lower rates of delayed gastric emptying [5, 11]. However, these trials focused on MIDP for all indications (benign, premalignant, and malignant) and included only a minority of patients with pancreatic ductal adenocarcinoma (PDAC). Therefore, these trials were insufficient to draw any conclusions on the oncological outcome of the minimally invasive approach [5].

The oncological safety of MIDP remains a subject of debate which hampers its further implementation [12, 13]. A European survey on minimally invasive pancreatic surgery demonstrated that 73% (*n* = 148) of surgeons from 27 countries regularly performed MIDP [14]. Less than half of these surgeons, however, performed MIDP for PDAC and 31% expected MIDP to be inferior to ODP concerning oncological outcomes [14]. Consequently, many patients affected by PDAC might not receive MIDP due to uncertainty regarding oncological safety, and these patients do not benefit from the potential advantages. In theory, this enhanced recovery could potentially improve the use of adjuvant chemotherapy compared to ODP, as shown for other pancreatic resections [15–17].

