### Data collection and patient follow-up

The required clinical data will be collected after randomization, i.e., from hospitalization up to 36 months postoperatively using standardized (online) case report forms (Castor EDC, CIWIT B.V., Amsterdam, the Netherlands) by the local treating physicians. All data is stored in an electronic database (Castor EDC, CIWIT B.V., Amsterdam, the Netherlands). Data monitoring is performed by the study coordinators who will crosscheck the case report forms with source data. Baseline characteristics (age, sex, performance status (Karnofsky score)), ASA physical status, body mass index, previous abdominal surgery, diabetes mellitus, preoperative imaging conclusion including tumor size and involvement of other organs and vessels, neoadjuvant treatment, serum levels of Hba1C, CA 19.9 and CEA, and baseline quality of life measures will be recorded before randomization. For all patients, the most recent preoperative imaging will be sent anonymously to the study coordinator. This will follow local ethical and privacy rules in every center. After completion of the study, all imaging modalities will be reassessed by two expert radiologists independently in order to define the preoperative pancreatic cancer stages. In case of disagreement between the expert radiologists, a third expert radiologist will be invited and discussion will take place until consensus is reached. The required clinical data will be collected after randomization, i.e., from hospitalization up to 36 months postoperatively using standardized (online) case report forms by the local treating physicians, and will be crosschecked with source data by the study coordinators. For quality of life, the EQ-5D-5L, QLQ-C30, and PAN-26 questionnaires are used. These will be sent to the participating patients at baseline, 14, 30, 90, and 180 days after surgery. Patients will also receive a questionnaire at 90 days and 365 days after surgery which focuses on readmissions, complications, body image, and adjuvant therapy. Patients will be followed up at the outpatient clinic every 6 months during the first 2 years after surgery and after 36 months after surgery (i.e., at 6, 12, 18, 24, 36 months). During these follow-up moments, patients will undergo an abdominal CT scan and serum levels of CA 19.9 and CEA tumor markers will be assessed.

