### Statistical aspects

#### Sample size calculation

The DIPLOMA trial is designed as a non-inferiority trial, hypothesizing that in patients with pancreatic cancer the rate of microscopically radical (R0) resection rate of MIDP is non-inferior to ODP. Based on data collected for the retrospective DIPLOMA cohort study (1377 patients, matched based on propensity scores) [18], the sample size is calculated with the following assumptions: 5% one-sided significance level (*α*), 80% power (1-*β*), expected R0 rate in the open group of 58%, expected R0 resection rate in the minimally invasive group of 67%, and a non-inferiority margin of 7%. Based on these assumptions, a sample size of 226 patients (113 patients per arm) is required. Including 2.5% drop-out after randomization (patients who undergo no surgery after randomization) and 10% metastasized disease leads to a total number of patients to be randomized of 258 (129 per study arm).

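### The sensitivity analysis for patient blinding excludes a narrower group than the one left unblinded, and length of hospital stay is left without a check

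*Protocol article*

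**What the plan says.** All points are in the protocol article.

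- **Who is not blinded (Blinding).** Patients at US centres, and blinding is also not done "in patients who are intra-operatively diagnosed with irresectable disease, such as metastases".
- **Why this is judged minor (Blinding).** "Since patient blinding only influences one of the secondary outcomes, time to functional recovery, and not the primary outcome".
- **The planned check (Blinding).** One sensitivity analysis, "excluding centers from the USA and patients with perioperative diagnosed metastasized disease will be performed for analysis of time to functional recovery".
- **How long blinding lasts (Blinding).** A large dressing hides the incisions until the functional recovery criteria are met, or until a medical reason requires earlier removal. A blinding index will measure how well the concealment worked.
- **Other outcomes (Secondary outcomes; Data collection and patient follow-up).** Length of hospital stay is a listed secondary outcome. Quality of life is measured with three patient questionnaires: "These will be sent to the participating patients at baseline, 14, 30, 90, and 180 days after surgery". A further questionnaire, which covers body image among other topics, goes out at 90 and 365 days.
- **Who is analysed (Randomization).** Only patients who have no surgery are dropped. All others, including those found metastatic at operation, are analysed by intention to treat.

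**The concern.** A sensitivity analysis meant to show the result among blinded patients should exclude exactly those who were not blinded. Here the unblinding rule covers irresectable disease of any kind, while the exclusion rule covers metastasised disease. An irresectable patient without metastases is caught by the first rule and missed by the second. Such a patient also did not have the planned resection, so their recovery time does not describe recovery after either type of pancreatectomy.

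The second problem is the claim that patient blinding matters for one secondary outcome only. If a patient's knowledge of the approach can shift time to functional recovery, it can shift length of stay, since the stay includes the days up to recovery. The protocol runs no check there.

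Time to functional recovery is named among the most important secondary outcomes, and the Discussion hopes to confirm the recovery results and shorter stay of two earlier trials. Those claims would rest on a check that is slightly mis-specified for one outcome and absent for the other.

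**Working it through.** **Step 1: the figures that exist.** The Blinding section states no number. The sample size was reproduced to see whether it is affected. Inputs from Sample size calculation: "5% one-sided significance level", 80% power, "expected R0 rate in the open group of 58"%, "expected R0 resection rate in the minimally invasive group of 67"%, margin 7 percentage points.

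- Per arm: n = (1.645 + 0.842)² × (0.58 × 0.42 + 0.67 × 0.33) / (0.09 + 0.07)² = 6.18 × 0.4647 / 0.0256 ≈ 112.2, rounded up to 113, so 226 in total. This matches.
- Inflation: 226 / (0.975 × 0.90) = 257.5, so 258. This matches.

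None of these inputs depends on patient blinding, because R0 is read by blinded pathologists.

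**Step 2: the two rules side by side.**

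| Patient | Unblinded by rule? | Excluded from the sensitivity set? |
|---|---|---|
| US centre | Yes | Yes |
| Non-US, metastases found at surgery | Yes | Yes |
| Non-US, irresectable without metastases | Yes | **No** |
| Non-US, resected | No | No |

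The third row is the mismatch. These patients had surgery, so the Randomization section keeps them in the analysis.

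**Step 3: how many.** The protocol expects 10% metastasised: 0.10 × 258 = 25.8, about 26 patients, who are excluded. It gives no share for irresectable disease without metastases. As an assumption, with 258 as the base:

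- 0%: 0 patients
- 1%: 0.01 × 258 = 2.6, about 3
- 5%: 0.05 × 258 = 12.9, about 13

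Any of these patients at a US centre would already be excluded, so these are upper figures for each assumed share. The number of US patients is not given either.

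**Step 4: which outcomes overlap with the blinded period.**

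- *Time to functional recovery* ends when the dressing may come off, so it lies within the blinded period unless the dressing is removed early. It is checked.
- *Length of hospital stay* contains those same in-hospital days, plus any days after recovery. It is not checked.
- *Quality of life* is first measured after surgery at day 14. A patient who has recovered by then has seen the wounds, in any centre.
- *Body image* is asked at 90 and 365 days, well beyond what the dressing is designed to conceal.

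Length of stay is therefore the one further outcome for which this check is clearly informative.

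**The case against.** **The affected group may be empty.** Eligibility requires a tumour expected to be radically resectable by both approaches, excludes involvement or abutment of major vessels, and asks for at least 5 mm from the celiac trunk. The sample size allows only for no surgery and for metastases. This stands as a limit on size: the set *can* contain unblinded patients, and the documents do not show that it *will*. The mismatch between the two rules remains.

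**Length of stay is not shown to be sensitive to patient blinding.** The Background reports "a 2-day reduction in both time to functional recovery and length of hospital stay" in earlier trials. That is a treatment effect and says nothing about bias from unblinding. Treating staff are not listed among those blinded, so excluding US centres does not remove bias through the discharge decision. Both remarks are fair. What remains is a route through the patient during the dressing period, which is the route the protocol accepts for functional recovery.

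**A reader might infer that quality of life and body image need the same sensitivity analysis.** The documents do not support this. Blinding is designed to end at functional recovery, so these outcomes are largely open-label everywhere, and dropping US or irresectable patients would not yield a blinded comparison. The same design makes the protocol's focus on functional recovery partly defensible.

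**A reader might also infer that the check ignores the US centres.** It does not; they are excluded.

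**Further sensitivity analyses belong in the statistical analysis plan.** That plan is promised and not shown, and it may cover length of stay. The mismatch and the absolute claim, however, are stated in the protocol text itself.

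**Conclusion.** The point holds in a limited form. The rule for leaving patients unblinded is wider than the rule for excluding them, so non-US patients who are irresectable without metastases can remain in a set meant to be free of unblinded patients. Under an assumed share of 0% to 5%, that is 0 to about 13 of 258; the true number is not given and may be zero. The statement that blinding influences a single secondary outcome is too absolute, because length of stay shares the blinded in-hospital period and is left unchecked.

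The documents do not show that any reported benefit would be biased, nor in which direction. The primary outcome, its analysis and the sample size are unaffected. This is a minor correction.

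**What to change.** 1. Define the sensitivity set by the unblinding rule itself: exclude US centres and every patient found irresectable during surgery, for whatever reason.
2. Run that set for time to functional recovery and for length of hospital stay. Report the number excluded by arm and reason, since irresectability is established after randomisation.
3. Replace the claim that a single secondary outcome is affected. Say instead that patient blinding can influence outcomes accruing while the dressing is in place, including functional recovery and length of stay.
4. Do not rerun the set for quality of life. State that patient-reported outcomes collected after dressing removal are open-label.

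The cost is a few changed phrases, one extra run on outcomes already collected, and a slightly smaller sensitivity set. The statistical analysis plan, due before database lock, can carry all of it.

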### General treatment regimen

Because of the pragmatic design of the DIPLOMA trial, there are no restrictions regarding postoperative care, blood tests, drain management, the use of medication, or other kinds of co-intervention. However, the participating centers should provide the same postoperative care for both study arms (MIDP and ODP), based on enhanced recovery principles, which include early mobilization and expanding oral intake as desired by the patient. The treating team will be asked to specify the use of this kind of additional (surgical) proceedings and medication in the online case report forms.

### Primary outcome

The primary outcome is the microscopically radical resection margin (R0) (including the transection and posterior margins (surgical margins), but excluding the anterior and superior/inferior margins/surface (anatomical margins)). R0 is defined as a distance between the margin and the tumor of ≥ 1 mm [32]. A standardized histopathology assessment protocol and corresponding online webinar showing the standardized histopathological assessment methods has been developed by expert hepato-pancreato-biliary pathologists from large pancreatic surgery centers participating in the trial. Pathologists from all participating centers will complete this webinar before participation in the trial. This protocol is based on recent and relevant literature and was agreed on by all participating pathologists. Histopathological assessment within the DIPLOMA trial is only performed by the pathologists who completed the webinar. In order to ensure uniformity, study coordinators will be present in all centers during surgery of the first patient and subsequent handling of the specimen by the pathologist. Also, a validation will be performed by reviewing 10% of specimens by external pathologists. Involved pathologists will be blinded for the applied surgical approach.

### Secondary outcomes

The most important secondary outcomes are overall survival, time and site of disease recurrence, and postoperative time to functional recovery. Other secondary outcomes of this trial include intra-operative parameters (type of surgery (laparoscopic or robot-assisted), conversion, method of pancreatic transection, vessel resection, operative time, blood loss, and blood transfusion) and postoperative outcomes (major complications, delayed gastric emptying, pancreatic fistula, post-pancreatectomy hemorrhage, surgical site infection, serum levels of CA 19.9 and CEA, postoperative intervention, intensive care unit admission, organ failure, length of hospital stay, readmission, (time to) start of adjuvant therapy). Additional to the primary outcome, other pathology outcomes are recorded, such as tumor size, specimen length and weight, histology grading, distance from the tumor to all margins, number of retrieved lymph nodes, number of positive lymph nodes, lymphovascular and perineural tumor invasion, and venous and arterial tumor involvement. For the economical evaluation, costs (intra-operative and postoperative costs) and quality of life are assessed.

### Data collection and patient follow-up

The required clinical data will be collected after randomization, i.e., from hospitalization up to 36 months postoperatively using standardized (online) case report forms (Castor EDC, CIWIT B.V., Amsterdam, the Netherlands) by the local treating physicians. All data is stored in an electronic database (Castor EDC, CIWIT B.V., Amsterdam, the Netherlands). Data monitoring is performed by the study coordinators who will crosscheck the case report forms with source data. Baseline characteristics (age, sex, performance status (Karnofsky score)), ASA physical status, body mass index, previous abdominal surgery, diabetes mellitus, preoperative imaging conclusion including tumor size and involvement of other organs and vessels, neoadjuvant treatment, serum levels of Hba1C, CA 19.9 and CEA, and baseline quality of life measures will be recorded before randomization. For all patients, the most recent preoperative imaging will be sent anonymously to the study coordinator. This will follow local ethical and privacy rules in every center. After completion of the study, all imaging modalities will be reassessed by two expert radiologists independently in order to define the preoperative pancreatic cancer stages. In case of disagreement between the expert radiologists, a third expert radiologist will be invited and discussion will take place until consensus is reached. The required clinical data will be collected after randomization, i.e., from hospitalization up to 36 months postoperatively using standardized (online) case report forms by the local treating physicians, and will be crosschecked with source data by the study coordinators. For quality of life, the EQ-5D-5L, QLQ-C30, and PAN-26 questionnaires are used. These will be sent to the participating patients at baseline, 14, 30, 90, and 180 days after surgery. Patients will also receive a questionnaire at 90 days and 365 days after surgery which focuses on readmissions, complications, body image, and adjuvant therapy. Patients will be followed up at the outpatient clinic every 6 months during the first 2 years after surgery and after 36 months after surgery (i.e., at 6, 12, 18, 24, 36 months). During these follow-up moments, patients will undergo an abdominal CT scan and serum levels of CA 19.9 and CEA tumor markers will be assessed.

### Definitions

Functional recovery is reached when all of the following criteria are met: adequate pain control with only oral analgesia, restoration of mobility to a level of independence, ability to maintain sufficient caloric intake (a minimum of 50% of the required daily intake), no need for intravenous fluid administration and no signs of active infection (no fever or other clinical symptoms) [5, 29]. Complications are classified using the Clavien-Dindo score [33]. Major complications are defined as a Clavien-Dindo grade III or higher. Postoperative pancreatic fistula [34], delayed gastric emptying [35], and post-pancreatectomy haemorrhage [36] are classified the International Study Group on Pancreatic Surgery (ISGPS) definitions and only grade B and C complications will be recorded. Surgical site infection is classified according to the Centers for Disease Control and Prevention definition [37]. TNM staging is classified according to the American Joint Committee on Cancer (AJCC) classification (8th edition) [38].

